#### Condition B: Waiting list concomitant with treatment as usual

Treatment as usual consists of treatment with ADHD medication for most patients. Additionally, certain patients would normally receive counseling or psychotherapy, although this is not systematically provided to every patient; thus, the randomization procedures are necessary to reduce this as a possible bias. If needed, patients are also offered assistance with regard to economy, housing, education, and work as well as contact with family and their network. The participants allocated to the waiting list control group were told to live as normal and continue with treatment.

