### Data and measurement

Clinical symptoms and function will be measured at the time of recruitment prior to randomization (T0), pre-intervention (T1), post-intervention (T2) as well as at 10 weeks follow-up (T3). The waitlist-control group will have two additional measurements during the pre- and post-waiting period. Measuring patient satisfaction and change in symptom load, general self-efficacy, quality of life, and function can serve as indicators of the preliminary efficacy of the intervention. The assessments and measurements are listed in Fig. 2.

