### Statistics

Statistical analysis will be conducted using SPSS [34] and STATA [35]. In order to calculate preliminary effects, chi-square statistics and *t* tests will be used for descriptive analyses of categorical and continuous variables, respectively, in addition to analysis of variance (ANOVA) for comparison of results for the control and experimental groups. Possible other predictors for the preliminary efficacy of psychoeducation will be examined using linear regression on the total sample (pre-post intervention). Intervention adherence will be calculated by assessing the response rate of participants receiving the intervention, response rate of returned questionnaires, and the number of sessions completed by intervention group participants. Recruitment and dropout rates will be evaluated using absolute and percentage frequencies.

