### Sample size

This project is intended to evaluate the feasibility of implementing an educational group intervention led in co-operation with health personnel and peer educators to inform an eventual larger-scale randomized study that will allow for a more rigorous assessment of the impact of the intervention. Hence, our sample size is driven primarily by practical issues related to the number of patients needed to enroll at each site, opinions about the questionnaires, and satisfaction with the intervention. Consequently, the anticipated sample will be 60 patients—30 patients in each arm. The chosen sample size is also in accordance with the median number of participants observed in an audit of pilot and feasibility trials in the UK [36].

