### Methodological weaknesses

This study is not double-blinded nor did we use the “placebo intervention” other than the waiting list owing to ethical considerations. We do not compare our model to another form of treatment other than treatment as usual, but this is because there is a lack of a gold standard for psychoeducational interventions in adult ADHD. The waiting list group design has certain weaknesses, but considering the ethical aspects requiring that all patients receive treatment, the interventions were important (waiting lists are typical in these clinics).

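### The pooled pre-post regression cannot identify predictors of efficacy: it has no untreated comparator and no predictor-by-arm interaction

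*Protocol article*

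**What the plan says.** The Statistics section of the Protocol article describes two separate analyses. The randomized comparison is by ANOVA: "in addition to analysis of variance (ANOVA) for comparison of results for the control and experimental groups". The predictor analysis follows: "Possible other predictors for the preliminary efficacy of psychoeducation will be examined using linear regression on the total sample (pre-post intervention". That sentence fixes a target (efficacy of psychoeducation), a method (linear regression) and a data set (everyone, before and after the intervention). It does not name the outcome variable, any arm term, any interaction or any baseline adjustment.

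Three other places show what the data set is likely to be:

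- Data and measurement defines the time points relative to the intervention: "pre-intervention (T1), post-intervention (T2) as well as at 10 weeks follow-up (T3".
- The same section gives one arm extra assessments: "The waitlist-control group will have two additional measurements during the pre- and post-waiting period".
- Methodological weaknesses justifies the waiting-list design by "considering the ethical aspects requiring that all patients receive treatment".

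Together these suggest that waitlist patients later take the programme and have their own pre- and post-intervention scores. The total sample before and after the intervention is then all patients over their own treated period.

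**The concern.** Efficacy is a difference between arms, so a predictor of efficacy must change the size of that difference. In a sample where everyone is treated, the association between a covariate and the pre-post result mixes three things: modification of the programme effect, the course the patient would have followed anyway, and, depending on the model, regression to the mean.

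Usual care is a concrete source of the second. The section on Condition B says that "certain patients would normally receive counseling or psychotherapy, although this is not systematically provided to every patient", and it relies on randomization to deal with the resulting bias. A pooled treated-only regression does not use that protection.

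At stake is the interpretation of one analysis. A factor that only marks a better or worse prognosis could be reported as marking who benefits from psychoeducation.

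**Working it through.** **Inputs from the documents.** The target, method and data set are as set out above. For sample size, "the anticipated sample will be 60 patients—30 patients in each arm", and 2 × 30 = 60. There is no power figure to reproduce: "our sample size is driven primarily by practical issues related to the number of patients needed to enroll at each site", and no alpha, power, SD or figure for this regression is given.

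**Assumptions, not from the documents.** Pre-post correlation *r* from 0.5 to 0.9 with equal variances; covariate correlation with change from 0 to 0.5; normal data; two-sided 0.05. All 60 patients are evaluable unless stated. In steps 2 to 4 the programme has no effect and nothing modifies it, so every flag is false as a predictor of efficacy. Each setting was simulated 4,000 times.

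**Step 1: what the coefficient estimates.** Let a covariate *x* have slope γ on the change that would have happened anyway, and slope δ on the programme effect.

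- Slope in treated patients: γ + δ.
- Slope in untreated waiting patients: γ.
- Difference, which is the arm-by-*x* interaction: δ.

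Only δ concerns efficacy. A pooled treated sample gives γ + δ. An arm main effect shifts the intercept but still leaves one common slope. Adjusting post for pre removes the part of γ that runs through the baseline score and leaves the rest.

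**Step 2: a purely prognostic covariate (δ = 0, 60 patients).**

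| Correlation of *x* with change | Pooled regression flags *x* | Arm-by-*x* interaction (30 v 30) flags *x* |
|---|---|---|
| 0 | 5% | 4.7% |
| 0.2 | 35% | 4.3% |
| 0.3 | 65% | 5.5% |
| 0.4 | 90% | 5.4% |
| 0.5 | 99% | 4.5% |

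Hand check at 0.3: atanh(0.3) × √57 = 0.310 × 7.55 = 2.34; 2.34 − 1.96 = 0.38; Φ(0.38) = 0.65.

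**Step 3: baseline severity as the predictor, raw change as the outcome, no baseline adjustment.** With equal variances, cov(change, baseline) = −(1 − *r*)σ² and var(change) = 2(1 − *r*)σ², so corr = −√((1 − *r*)/2). At *r* = 0.7 this is −√0.15 = −0.387. Fisher-z: atanh(0.387) × √57 = 0.408 × 7.55 = 3.08; 3.08 − 1.96 = 1.12; Φ = 0.87. The simulation agrees:

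| *r* | 60 evaluable | 45 evaluable (assumed) |
|---|---|---|
| 0.5 | 99% | 95% |
| 0.6 | 95% | 89% |
| 0.7 | 87% | 76% |
| 0.8 | 70% | 58% |
| 0.9 | 41% | 31% |

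The arm-by-baseline interaction is flagged in 4.5% to 5.3% (*r* = 0.5, 0.7, 0.8).

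**Step 4: a covariate linked only to the baseline score (correlation 0.3 or 0.5; *r* = 0.6 or 0.7).** It is flagged in 14% to 43% when change is regressed without baseline, and in 4.4% to 5.3% when post is adjusted for pre. Baseline adjustment closes this route but not that of step 2.

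**Step 5: what the interaction test can detect with 30 v 30.** Power is 19%, 45% and 83% for slope differences of 0.3, 0.5 and 0.8 residual SD of change per SD of the covariate.

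**The case against.** The strongest reply is that the regression is described in one sentence of a condensed article, and the model form may be settled in an analysis plan that is not shown. The outcome could be T2 with T1 as covariate. Predictors described as *other* ones, mentioned straight after the between-arm ANOVA, could mean that arm is also in the model. This stands as far as it goes: raw change without adjustment is an inference, and the results of step 3 hold only under it. A reader might take the 87% at *r* = 0.7 as the size of the problem, or conclude that the analysis is bound to return regression to the mean as a predictor. The documents do not support either. That figure needs a raw-change outcome, baseline severity of the same outcome as the predictor, no baseline adjustment, a 0.05 filter and 60 evaluable patients. None of the first four is stated, and 60 is the anticipated enrolment, with dropout expected to be reported. An unrelated covariate is flagged at the nominal 5%.

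The reply does not rescue the label. With T1 adjustment, or with an arm main effect, the coefficient is still prognostic (steps 1 and 2). The target and the data set are stated, not left open, and they do not match.

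It is also fair that the sentence is hedged as possible predictors of preliminary efficacy, and that the ANOVA is a separate analysis, so the estimate of the arm difference is untouched. That limits the consequence. It does not make the regression answer the question put to it.

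**Conclusion.** The point holds. Followed as written, the analysis would report prognostic associations as predictors of the efficacy of psychoeducation. This rests on reading the total sample as both arms' treated periods. If the sample were instead the randomized period with arm in the model, the conclusion would be the same unless a predictor-by-arm interaction were fitted.

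The size depends on assumed correlations. False flags run from 35% to 99% for prognostic covariates correlated 0.2 to 0.5 with change. For baseline severity they run from 41% to 99%, but only under unadjusted raw change with 60 evaluable.

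A reader might infer that false predictors would go on to shape eligibility or stratification in the main trial. The documents do not say so. The section on the main study and the decision to proceed rests that decision on client satisfaction and on preliminary efficacy for ADHD symptoms and quality of life, and gives predictor results no role. Stratifying on a factor that is only prognostic is legitimate in any case. The importance is therefore moderate: a secondary analysis whose stated interpretation should be corrected.

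**What to change.** Choose one of two changes to the Statistics section.

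1. **Keep the question about efficacy.** Over the randomized period (intervention arm pre to post intervention, waitlist arm pre to post waiting), regress the follow-up score on arm, the predictor, the predictor-by-arm interaction and the baseline outcome. Do this for a short list of predictors named in advance. Report each interaction as an estimate with 95% CI and label the analysis exploratory. The extra waitlist assessments already planned supply the data.
2. **Keep the pooled regression.** Model the T2 score with the T1 score as covariate, and report the results as predictors of outcome after the programme, not of its efficacy.

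Both cost only analysis wording, with no new patients or assessments. The first has a statistical price: with 30 per arm the standard error of the slope difference is about √(1/30 + 1/30) = 0.26 residual SD per SD of the covariate. Its 95% CI is then about ±0.5, so only large modification would be seen. The second gives up any statement about who benefits from the programme.

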### Sample size

This project is intended to evaluate the feasibility of implementing an educational group intervention led in co-operation with health personnel and peer educators to inform an eventual larger-scale randomized study that will allow for a more rigorous assessment of the impact of the intervention. Hence, our sample size is driven primarily by practical issues related to the number of patients needed to enroll at each site, opinions about the questionnaires, and satisfaction with the intervention. Consequently, the anticipated sample will be 60 patients—30 patients in each arm. The chosen sample size is also in accordance with the median number of participants observed in an audit of pilot and feasibility trials in the UK [36].

### Ethics

The project is registered and approved by the Regional Committees for Medical Research Ethics (REC 2016/1885) and will be conducted in accordance with the ethical principles of the Declaration of Helsinki (2013).

### User involvement

User involvement will be by advisory participation by one peer educator from the ADHD user organization with experience cooperating with mental health services. The advisory participation will occur during protocol preparation to ensure that all relevant outcomes are included. User involvement will also be determined during the intervention delivery phase. Peer educators will be co-led via two sessions.

## Discussion

This study protocol presents a pilot randomized, waitlist-controlled, multicenter trial of a psychoeducational group intervention for patients with ADHD. ADHD is a disorder with high prevalence rates associated with impaired psychosocial functioning, education, and work. Patients may therefore require education and support to cope with these conditions during everyday life. However, the effectiveness of such programs implemented in outpatient clinics remains unclear. This pilot study will assess the preliminary efficacy of the intervention on ADHD-related symptoms (ASRS and SCL-9), ADHD-related quality of life, function, and employment status as well as patient satisfaction with intervention content. If the program is beneficial for the patients and feasible for the clinics, then it may be implemented in other clinics. The results would also add to the preliminary empirical evidence needed to inform the development of larger and more complex studies.

### Main study and decision to proceed

The pilot study utilizes the same design as the intended main study to make a proper decision on whether to proceed or not. The decision to proceed will be based on the measurement of client satisfaction as well as the preliminary efficacy of ADHD-related symptoms and quality of life. With this, our study may influence the clinical practice and short-term results to empower patients in the management of their own symptoms and health treatment. The short-time impact of the intervention on function is unclear. If the decision is to proceed, then the long-term effects of the intervention will be assessed in a new main study employing the same design but with an additional 3 or 6 months of follow-up.

### Methodological strengths

To the best of our knowledge, this will be the first pilot randomized, waitlist-controlled, multicenter trial of a psychoeducational intervention for patients with adult ADHD. All participants will be recruited from outpatient clinics. These are patients with a confirmed diagnosis. The treatment is delivered in outpatient clinics and will therefore increase the ecological validity of the study within a Norwegian health care context. The outcome measurements will be based on validated instruments and well-tested in international research as well as in clinical practice. This offers useful data both for research and the clinic. Translated instruments are validated and published in international peer-reviewed journals. We used a multicenter intervention and different course leaders and lecturers to reduce the effect of individual therapeutic factors. This offers more reliable evidence on the specific effects of the intervention content.

### Methodological weaknesses

This study is not double-blinded nor did we use the “placebo intervention” other than the waiting list owing to ethical considerations. We do not compare our model to another form of treatment other than treatment as usual, but this is because there is a lack of a gold standard for psychoeducational interventions in adult ADHD. The waiting list group design has certain weaknesses, but considering the ethical aspects requiring that all patients receive treatment, the interventions were important (waiting lists are typical in these clinics).

## Conclusion

This study protocol presents a pilot randomized, controlled trial that will evaluate an innovative education program for patients with ADHD. It aims to enhance self-management behaviors. The results will be of interest to health care professionals working with ADHD patients. Additionally, our study will be of value to user organizations and policy makers administering educational programs with respect to the agenda of prevention and treatment of ADHD in adulthood.
